### Randomization and masking

Randomization in the three groups occurred after screening and baseline assessment (T0). Subjects were randomly assigned to SST or MCNT or no treatment. The randomization process was performed using a computer algorithm (http://graphpad.com/quickcalcs/randMenu/) by an independent operator not involved in neither phase of our research. All evaluations in both pre- and post-treatment are conducted by two psychologists blind to group allocation.

### Intervention

Our study involves two types of intervention: the MCNT, which represents the experimental intervention; and the SST, the treatment as usual (TAU). Both treatments last for nine months and provide regular meetings between the professionals responsible for the treatment and the families and the teachers of the children. Regular weekly meetings among professionals are also included in both treatments. The MCNT is based on a multidimensional approach with children working in small groups while the SST is domain specific and treatment is one-on-one based.

#### Experimental treatment: The movement cognition and narration of the emotions treatment (MCNT)

The MCNT is an intervention in which children work in small groups, for 3 h each day, five days a week, Monday through Friday, for nine months. Each day they arrive at 2 pm, with a shuttle that brings them from their school to our Centre. They are divided into 3 groups, for the whole treatment, named Red, Blue and Green, according to their global functioning, grade and/or special educational needs. Upon arrival children are gathered all together for a 15 min long relaxing activity, after which each group starts with one of the three laboratories for 45 min. At the end of the first, the three groups switch the activity until all groups have completed all three laboratories.

MCNT is focused on the three domains affected in children with BIF that are strictly embedded with learning abilities: motor, cognitive and socio-emotional domain. This treatment consists of: a) Movement training to improve motor planning and fine and gross motor abilities with a Game Therapy approach using the Wii and Xbox video game platforms; b) Cognitive training for the empowerment of the executive functions such as working memory, planning abilities, problem solving, reasoning with the use of the multimedia interactive whiteboard (MIW); and c) an emotive training to learn how to Narrate the emotions to help the child to cope with the experiences of her/his daily life.

We chose to use the technology devices mentioned above because they are able to capture the attention and are highly motivating for the child. In addition, the use of the MIW represents a very useful visual aid for a visually-oriented teaching strategy that is effective in fostering verbal comprehension, memory encoding and storage processes. With both devices, moreover, it is possible to promote small competitions between the children which are very effective in motivating the child and improving information speed processing, positive interdependency and frustration tolerance. Finally, to help the child to narrate the emotions, a psychotherapist promotes several activities such as the narration of fairy tales, or drawing and symbolic playing to create a new story, to promote the capacity to think, to recognize and to master the emotions.

The first level concerned the movement execution and planning abilities: the objective is to improve balance, fine and gross motor abilities, hand-eye coordination, impulsive motor response inhibition, praxic abilities and attention. For this intervention, the Nintendo Wii Console with the “Wiimote” and the “balance board”, and the “Xbox 360 Kinetic” platforms were used. A game therapy approach is used to improve the children’s motivation and compliance. In the first weeks of treatment, the focus is on easier visual-motor integration skills, and the children familiarize themselves with the Wiimote while using it as a laser pointer to match a fixed visual input on the screen. A second step involves more complex games whereby the child points the Wiimote to a moving target (Wii Motion Plus game) that requires an increased involvement of attention and higher visual-motor integration ability. A third step involves games such as Wii Sports in which children use both the Wiimote and the Wii Balance board to train balance and coordination of both upper and lower limbs. Also, Wii Music and Wii Party games are used to train rhythm, timing of movement and inhibition of impulsive motor behavior. During the whole process, advanced executive functions, such as planning competence, working memory and inhibitory control are involved and trained so as to render the movements more fluid, economical, quicker and functional. Finally, the Xbox Kinetic console is used to train not only all body segments motricity but also moving in unison with another child. For example, in the Kinetic Adventure game, children maneuver a boat on river rapids in pairs with the movements of their bodies. In this step, the child needs to continuously adjust his/her own position in response to the movements of the other person. This activity facilitates training the awareness of his/her own body in space and relative to the other along with the capacity to master a novel situation in a cooperative manner.

The second domain concerns the cognitive abilities. The cognitive training is focused on several domains that include language comprehension and expression and executive functions, such as deductive and inductive reasoning, working memory, planning and problem solving, attention and concentration, inhibition of impulsive verbal responses. This part of the MCNT involves the use of the MIW. Particular attention is devoted to finding appropriate strategies to solve problems and to the constant training of the abilities to increase the velocity with which the task is executed. The aim is to promote the ability to explore the information, to select salient features which are relevant to solve the problem and finally to take a decision while examining the possible choices. Moreover, children are trained at keeping and sharing their attention with all members of the group for the whole duration of the session by promoting their active participation in the activities. Finally, according to the incremental intelligence theory [64], children are supported in the idea that their intelligence and their capacities can be increased by training and that each child has a different way to learn and to encode sensorial stimuli: some rely more upon visual strategies while others prefer verbal modalities. Indeed, great attention is devoted to the cognitive style and the learning strategies of each child. This approach helps the child to focus on the discovery of his/her personal functioning rather than being worried about the grade. Finally, working in a group promotes prosocial behavior and cooperative learning.

The third domain concerns emotions and social skills. BIF children very often lack adaptive skills and show behavioral, emotional and/or social-relations problems. The focus of this part of the treatment is to help the children to express, recognize and cope with their own emotions. We named this process “alphabetization” of the emotions [65]. The underlying idea stems from the psychoanalytic model of Bion [66, 67] in which the comprehension of the emotional experience is central to thought and learning. The term “alphabetization” refers to the capacity to transform the unknown sensations that precede and accompany any emotion into elements that can be thought and narrated [66, 67]. This process demands that the unknown sensations, which can generate discomfort, can be tolerated and contained in the mind of the subject and/or of the therapist for a sufficient time to be transformed into symbols that can be thought, experienced and communicated [65]. The alphabetization process operates through a symbolization mechanism that implies the “as if” process. Giving a simple name to the emotion is not sufficient, it is necessary to transform it into a metaphor, a story or a play. Such a process is very important for social relations: if the child can express his/her inner states, he/she has no need to act rashly upon them. Finally, the alphabetization process helps the child to “clear” the mind from very unwanted thoughts and sensations, which can ultimately facilitate the cognitive processes. The therapist, a psychologist with a psychotherapy degree, uses different approaches to promote the narration of the emotions: symbolic play, reading, inventing and/or dramatizing a story, drawing and talking. These activities are considered creative processes with a transitional function [68] that enable the children and the therapist to deal with the emotions in an indirect way, preventing the fear of being judged and persecutory feelings. Finally, such a transitional space enables and promotes the “as if” process [68]. The therapist helps the children to associate the feelings and emotions narrated and symbolized through the activities with their own experiences. Within the group, each child can introduce new characters, new scenarios and/or situations to challenge the group to find solutions. The goal is to encourage cooperation and to experience the facilitation effect of the group in thinking and coping with emotions.

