## Methods

### Study design

This is a multicentre interventional single blind randomized controlled study with three groups of children with BIF: group 1- children treated with SST (conventional treatment; *N* = 20); group 2-children treated with the MCNT (experimental treatment, *N* = 20); group 3-children not treated -on the waiting list for SST (no treatment *N* = 20).

The Study was approved by the Ethics Committee of the Don Gnocchi Foundation and of the ASST S. Paolo and S. Carlo Hospital.

All parents signed a written informed consent at the first meeting.

The primary and secondary outcome measures are determined at two time points, within two months prior to the beginning of the treatment (T0) and within two months after the end of the treatment (T1). Evaluations of all children made before and after treatment are performed by two psychologists blind to the type of intervention that the child receives. The flow diagram for study enrollment and randomization, as per Consolidated Standards Of Reporting Trial (CONSORT) guidelines, is shown in Fig. 1.

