### Participants

Sixty participants will be consecutively recruited from the Child and Adolescent Neuropsychiatry Unit of IRCCS Don Carlo Gnocchi Foundation and of the ASST S. Paolo and S. Carlo Hospital.

Inclusion criteria are: age range between 6 to 11 years old and attending primary mainstream school; with a Full Scale Intelligence Quotient (FSIQ) score ranging from 70 to 85 determined with the Wechsler Intelligence Scale for Children-III (WISC-III) [52, 53]; presence of learning disabilities assessed with the standardized test battery for developmental dyslexia and dysorthographia (DDE-2) [54] and dyscalculia (AC-MT 6–11) [55]; difficulties in executive functions and or verbal comprehension assessed with Modified Barrage bell test (MBT) [56],Tower of London (TOL) [57, 58], and the Test of Reception of Grammar (TROG 2) [59, 60]; presence of an impact on daily life of the above mentioned difficulties as measured by the Child Behavioral Checklist (CBCL 6–18) [61, 62] and Vineland 2 [63].

The exclusion criteria are: presence of major neuropsychiatric disorders (such as ADHD and autism spectrum disorder); presence of neurological conditions such as epilepsy, traumatic brain injury, brain malformations and infectious disease involving the central nervous system. Moreover, the presence of systemic diseases such as diabetes or dysimmune disorders, genetic syndromes such as Down syndrome or Fragile X syndrome and a positive history for psychoactive drugs, particularly referring to current or past use of psychostimulants, neuroleptics, antidepressants, benzodiazepines and antiepileptic drugs are also considered exclusion criteria.

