### Analysis

Statistical analyses on outcome measures will be conducted using R and SPSS. The General Linear Model (GLM) will be used to test the interaction effects between treatment (MCNT vs no treatment, MCNT vs TAU, TAU vs no treatment) and time (2 repeated measures, T0 and T1). Violations of the parametric model assumptions will be tested and explored with ad-hoc techniques. If violations will be detected, robust methods, data manipulation or statistical corrections will be applied accordingly. An intention-to-treat analysis approach will be used. The missing data process will be examined and the proper imputation method will be selected thereafter.

MRI data will be analyzed with specific statistical software: SPM12, (http://www.fil.ion.ucl.ac.uk/spm/); and FreeSurfer (https://surfer.nmr.mgh.harvard.edu/) and FSL (https://fsl.fmrib.ox.ac.uk/fsl/fslwiki/). Random effect analyses will be done to detect if there is an effect of treatment on the variables measured. The model will comprise a between factor level (group) and a within factor level (time). Demographic characteristics will be used as covariates if associated with the outcome measure.

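### MCNT is delivered in three fixed groups, but the model and the power treat all 60 children as independent; if responses within a group are positively correlated, the MCNT contrasts look too precise

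*Protocol article*

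**What the plan says.** The section on the experimental treatment states that "children work in small groups, for 3 h each day, five days a week, Monday through Friday, for nine months", and that "They are divided into 3 groups, for the whole treatment, named Red, Blue and Green, according to their global functioning"; grade and special educational needs may also decide the group. Each group moves as a unit through the three laboratories every day. The same section presents group work as part of how the treatment acts: one goal is "to experience the facilitation effect of the group in thinking and coping with emotions".

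The Intervention section contrasts the two active arms: "children working in small groups while the SST is domain specific and treatment is one-on-one based". The third arm waits without treatment. Study design gives 20 children to each arm.

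Under Analysis, "The General Linear Model (GLM) will be used to test the interaction effects between treatment" and time. The MRI model has a between factor (read here as trial arm) and time. Neither model has a term for the MCNT treatment group. Sample size gives an effect size of 0.43 and a power of 0.83 for 60 children, with no design effect or ICC.

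**The concern.** This is a partially nested design: children in one arm spend nine months in fixed small groups, while children in the other two arms have no treatment group. Whatever makes one MCNT group gain more or less than another (its dynamics, its pace, a disruptive or helpful member) is shared by all its members. Their gains then carry less information than the same number of independent gains, and a model that ignores this understates the variance of the MCNT mean.

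The error would fall on the two contrasts that carry the trial's main claim, MCNT versus SST and MCNT versus no treatment, and it would favour declaring MCNT effective. SST versus no treatment would not be affected.

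**Working it through.** **Inputs from the article.** 20 children per arm (Study design); differences of 8 points (MCNT versus SST) and 10 points (MCNT versus no treatment) in FSIQ change, SD 10 (Sample size); three MCNT groups.

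**Assumptions.** Two-sided alpha 0.05; all 20 MCNT children treated at the same time, hence groups of 7, 7 and 6; ICC of the change score 0.02 to 0.20. The article gives none of these.

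**Step 1: reproduce the stated power.** The two differences imply mean changes of 10, 2 and 0, with overall mean 4.
- f = √[(6² + 2² + 4²)/3] / 10 = √18.67 / 10 = 0.432, which matches 0.43.
- One-way ANOVA on change, 60 independent children, noncentral F with 2 and 57 df: power 0.839, or 0.836 with f rounded to 0.43. This matches the stated 0.83 to within a point.

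The figure therefore contains no allowance for clustering. It is also the power of the overall three-arm test.

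**Step 2: design effect in the MCNT arm.**
- Effective group size = Σm²/20 = (49 + 49 + 36)/20 = 6.7.
- Design effect DE = 1 + (6.7 − 1) × ICC = 1 + 5.7 × ICC.

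**Step 3: standard error and type I error of an MCNT contrast.**
- Naive SE = 10 × √(1/20 + 1/20) = 3.16.
- True SE = 10 × √(DE/20 + 1/20), so the ratio is √[(DE + 1)/2].
- Actual type I error of the nominal 5% test ≈ 2 × [1 − Φ(1.96/ratio)].
- Power for 8 points, normal approximation = Φ(8/true SE − 1.96). It is 72% at ICC 0 (69% with the t distribution on 38 df).

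| ICC | DE | True SE | Ratio | Type I error | Power, 8 points |
|---|---|---|---|---|---|
| 0.02 | 1.11 | 3.25 | 1.03 | 5.7% | 69% |
| 0.05 | 1.29 | 3.38 | 1.07 | 6.7% | 66% |
| 0.10 | 1.57 | 3.59 | 1.13 | 8.4% | 61% |
| 0.20 | 2.14 | 3.96 | 1.25 | 11.8% | 52% |

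A simulation of 100,000 trials per ICC, with the error variance pooled over the three arms, gave 5.8%, 6.6%, 8.4% and 12.0% for MCNT versus SST. SST versus no treatment stayed between 5.0% and 5.2%.

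**Step 4: the same with two cohorts.** If the 20 children form six groups (4, 3 and 3, twice), effective group size = 68/20 = 3.4 and DE = 1 + 2.4 × ICC.

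| ICC | DE | Ratio | Type I error | Power, 8 points |
|---|---|---|---|---|
| 0.02 | 1.05 | 1.01 | 5.3% | 71% |
| 0.05 | 1.12 | 1.03 | 5.7% | 69% |
| 0.10 | 1.24 | 1.06 | 6.4% | 67% |
| 0.20 | 1.48 | 1.11 | 7.8% | 62% |

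**Step 5: does sorting by functioning matter?** MCNT children were sorted into 7, 7 and 6 on a baseline variable correlated 0.3 or 0.5 with the outcome, with no true group effect. The naive t test rejected about 5% of true nulls (5.1% and 5.2%), although the apparent ICC averaged 0.08 and 0.23. Sorting makes an observed ICC hard to interpret; it does not inflate the error.

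**Step 6: what a group-level test would cost.** With 7, 7 and 6, Satterthwaite df for MCNT versus SST (2 df for MCNT groups, 19 for the comparator) are about 6.6, 5.9, 5.1 and 4.2 at the four ICCs. Power for 8 points is then 56%, 51%, 44% and 35%.

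**The case against.** A reader might infer that the standard errors are certainly too small. The article does not support that. It gives no ICC, and at zero there is no error. The hope that children "experience the facilitation effect of the group in thinking and coping with emotions" is a therapeutic aim: if it works equally in all three groups, it raises the arm mean and belongs to the treatment effect. An ICC needs groups to differ in gain, and all three groups pass through the same laboratories. This stands, and the conclusion has to be conditional. The rationale makes a positive ICC plausible but does not fix its size.

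A reader might also take grouping by functioning as a further source of inflation. Step 5 shows that it is not.

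The 7/7/6 split is assumed. Since "Sixty participants will be consecutively recruited", children may enter treatment in successive cohorts, and more, smaller groups would shrink the problem. This stands too; step 4 shows it smaller but not gone.

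The Analysis section promises to test model assumptions and to apply robust methods or corrections, and an unseen analysis plan could add a group term. But that clause is generic. It does not name clustering or commit to recording group membership, and the power figure has already been computed under independence.

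Finally, a mixed model with a random MCNT group effect is the textbook remedy, but it suits this trial poorly as the primary analysis. Groups formed by functioning are not exchangeable, three of them estimate a variance badly, and the loss of df in step 6 is heavy. In the sorting simulation, a group-level test with Satterthwaite df, unadjusted for T0, rejected only 2.4% and 1.2% of true nulls. This objection to the remedy stands.

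**Conclusion.** The point holds in conditional form. The design is partially nested, and both the stated model and the stated power ignore it. If the ICC of change within MCNT groups is positive, the two MCNT contrasts are reported as more precise than they are. Under the assumptions in the working, the understatement runs from slight (SE ratio 1.03, type I error 5.7% at ICC 0.02) to material (1.25 and 11.8% at ICC 0.20) with three groups, and from 5.3% to 7.8% with six. The direction follows from the design; the size rests on an ICC and a cohort structure that the article does not give. The trial is described as ongoing, so a remedy can still be put in place.

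**What to change.** - Record each child's MCNT group and cohort in the trial data.
- Keep the planned treatment-by-time comparison. Report every MCNT contrast also with its standard error inflated for a prespecified range of ICCs, for example 0.02 to 0.20, using the group sizes that actually occurred. State whether the conclusion changes anywhere in that range.
- State that the power of 0.83 assumes no clustering, and give the power over the same range.
- If a partially nested mixed model with small-sample df is fitted, present it as supportive only.

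The work is small: two recorded variables and a short sensitivity table. The cost is wider intervals for the MCNT contrasts and a less favourable power statement. No child's treatment is affected.

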#### Treatment as usual: The standard speech therapy (SST)

STT is an individual treatment consisting of two 45 min sessions each per week for nine months. The focus is on the training of the academic abilities that are compromised in the child as assessed by the neuropsychological evaluation at T0 (pre-treatment). Typically, the skills mostly affected are reading comprehension, word-meaning relationship (semantics); writing problems related to phoneme-grapheme correspondence; arithmetic abilities; and problem solving. To empower these skills, SST uses both pencil/paper tools and specific rehabilitation software (http://www.erickson.it/). In the event of dyslexia or dysorthographia, the principal aims of SST are to increase processing information speed and transcoding, reducing spelling mistakes and expanding personal vocabulary. One of the approaches used is sub-lexical treatment. For dyscalculia, images are used to reason and solve the problem as, for example, in the analogical method [69]. Moreover, the empowerment of transversal competences such as phonological competences, perception, visual-spatial ability, attention, memory and other executive functions is pursued together with the use of compensative tools. Key criteria are functional re-education and the use of a meta-cognitive approach. The first provides for using alternative/different strategies to cover or partially rehabilitate compromised mechanisms whereas the second is based on strategies to focus the attention on mental processing (input, elaboration and output). Finally, the speech therapist offers pedagogy consultation for both parents and teachers to increase their knowledge concerning learning difficulties and potentially associated behavioral-emotional problems and finally to share effective problem solving strategies.

#### Assessment design and outcomes measures

The timeline of the study is illustrated in Fig. 2. All children are evaluated at two time points, within two months prior to the beginning of the treatment (T0) and within two months after the end of the treatment (T1). For the no-treatment group the same time interval is kept.

To measure intellectual functioning and motor competences, we used the WISC-III [52, 53] and the Movement Assessment Battery for Children (M-ABC) [70], respectively.

The Emotional Quotient Inventory-Youth Version (EQ-i:YV) [71] was used to assess the emotion competences, while the Child Behavior Check List (CBCL 6–18) [61, 62] and Vineland 2 [63] were employed for investigating adaptive behavior.

A full neuropsychological evaluation was also made with the use of following tests: the Modified Bells Test (selective attention MBT) [56]; the Tower of London (TOL) planning ability and inhibitory control; [57, 58]; the Neuropsychological Evaluation Battery for developmental age 5–11 (BVN5–11, speech fluency, selective word retrieval and Corsi) [72] to assess verbal executive function and verbal and visual short term memory; the Test of Reception of Grammar-2 (TROG2, language comprehension) [59, 60].

Finally, our study includes measures of brain morphometry and function, evaluated by means of magnetic resonance imaging (MRI) as surrogate outcome measure. All children participating in the study are evaluated with non-conventional brain MRI to investigate brain morphometry and functionality in the regions that we found abnormally developed in our previous work [25]: the parahippocampal, temporal and sensory-motor cortices.

